### Confidentiality {27}

Computer-based records for all research participants (Veteran and non-Veteran) are maintained through the VA Computerized Patient Record System (CPRS), a secure network with password protection, with access provided only to research personnel who are approved by the institutional review board. A unique study identification number is used in lieu of personal identifiers on study records. Consent and privacy authorization forms that contain personal identifiers are stored in locked filing cabinets located in locked offices in approved locations with the research centers. Data will be destroyed according to the Records Control Schedule per VA guidance.

### Plans for collection, laboratory evaluation, and storage of biological specimens for genetic or molecular analysis in this trial/future use {33}

Not applicable. No genetic or molecular analyses are planned during the trial or in the future.

## Statistical methods

### Statistical methods for primary and secondary outcomes {20a}

#### Primary comparative analyses

Our primary analysis will assess the intention-to-treat (ITT) effect of the integrated behavioral therapy program (integrated nocturia and insomnia intervention program) on nocturia frequency compared to the health education group (the primary outcome is single item from ICIQ-OAB 4 months post-randomization). The ITT approach is the standard approach for intervention evaluations in a randomized trial and will include all the randomized participants, including dropouts and non-adherent participants, in the analyses to ensure valid group comparisons. (Generalized) linear mixed effects models (G)LMMs will use all available data from all the randomized participants based on less stringent assumption than completed case analyses. The analyses will adjust for the stratified randomization variables (study site and sex) as suggested in the statistical literature that failure to adjust variables used in the randomization process can result in large *P* values and wide confidence intervals [64]. We expect that the covariates (age, sex, race/ethnicity, education, socioeconomic status, and clinical measures [i.e., presence of nocturnal polyuria or obstructive sleep apnea]) will be balanced between the intervention and control groups at baseline by randomization. However, if by any chance, there are any baseline covariates imbalanced between the intervention and control groups, they will be included in the (G)LMM fixed effects to control for potential confounding.

Aim 1/Hypothesis 1: *Compared to control, participants assigned to the integrated nocturia and insomnia behavioral intervention will demonstrate a greater reduction in nocturia frequency over 4 months*. The primary outcome of nocturia frequency will be measured as the average episodes per night at baseline, 1 week after intervention (approximately 2 months), and 4 months through the ICIQ-OAB questionnaire’s nocturia item. An LMM will be used to evaluate the group difference over time in average nocturia frequency per night, with group (the integrated intervention vs. control), time, time*group interaction, and stratified randomization variables (study site and sex) in fixed effects, and nested two-level random effects to account for correlations due to clustering by study site and participants. The time*group interaction will provide the estimated ITT effect of the integrated intervention on nocturia frequency over time. Imbalanced baseline variables, if any will be included in the LMM.

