### Sample size {14}

Power calculations are informed by parameter assumptions derived from past clinical trials of behavioral interventions for lower urinary tract symptoms and/or sleep disorders conducted by our study team members or consultants, corroborated by trends in our previous integrated nocturia and insomnia intervention feasibility study [36, 37, 55]. We assume an average frequency of at least 16 nocturia episodes per week (~ 2.3 episodes/night) in our baseline trial population, and an average decrease in nocturia frequency of 2 episodes per week (~ 0.3 episodes/night) over 4 months in the control group, given a recent systematic review including 17 trials assessing placebo-response in studies of treatments for nocturia [56]. We also anticipate a clinically meaningful reduction in nocturia frequency (item from the ICIQ-OAB) in the integrated nocturia and insomnia intervention group of at least 7 episodes per week (~ 1 episode per night) over 4 months, leading to a between-group difference in improvement in nocturia frequency of 5 or more episodes per week (0.7 episodes/night) between the integrated nocturia and insomnia intervention and control arms. This effect size represents a meaningful threshold of improvement in nocturia frequency that can be communicated to patients and clinicians, and corresponds to a clinically meaningful improvement of greater than half a standard deviation in the mean nightly nocturia frequency given a range of potential standard deviations [56, 57]. Using an approximation of the covariance matrix of the regression coefficients of the proposed linear mixed effects models (LMMs), we estimate that a sample of 192 participants, randomized in equal proportions to the two arms, will provide > 80% power in 2-sided tests with an experiment-wise type-I error rate of 5% [58], to detect the proposed greater reduction in nocturia frequency of least 5 episodes/week (0.7 episodes/night) associated with integrated intervention versus control intervention, assuming a cumulative loss to follow-up level of less than 15% accumulated at roughly equal rates between sequential follow-up visits. The assumption of loss-to-follow-up < 15% is based on our existing integrated intervention feasibility study, as well as prior trials of behavioral treatment programs for urologic symptoms conducted by the investigators in which early termination was < 15% over similar time periods [36, 37].

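### Baseline covariates beyond site and sex enter the primary model only if found imbalanced, with no criterion, so the final model is settled after the arms are compared

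*Protocol article*

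**What the plan says.** All of this is in the protocol article, Statistical methods {20a}, Primary comparative analyses, unless another section is named.

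- **Always in the model:** "The analyses will adjust for the stratified randomization variables (study site and sex").
- **Expected to balance by randomization:** "the covariates (age, sex, race/ethnicity, education, socioeconomic status, and clinical measures [i.e., presence of nocturnal polyuria or obstructive sleep apnea"]). That is seven variables, one of which is sex.
- **The conditional rule:** if "there are any baseline covariates imbalanced between the intervention and control groups, they will be included in the (G)LMM fixed effects". The stated purpose is control of potential confounding.
- **The rule repeated for Aim 1:** "Imbalanced baseline variables, if any will be included in the LMM". No list is given there.
- **The primary model:** nocturia is "measured as the average episodes per night at baseline, 1 week after intervention (approximately 2 months), and 4 months", and all three values are responses in a linear mixed model. The treatment effect is defined thus: "The time*group interaction will provide the estimated ITT effect of the integrated intervention on nocturia frequency over time".
- **A second description of the effect:** Outcomes {12} gives the primary metric as mean nocturia frequency at 4 months after randomization and mentions neither change nor an interaction.

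The article does not say what counts as imbalanced, or whether a flagged covariate enters as a main effect or is also crossed with time.

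**The concern.** The article itself expects balance because of randomization. Any imbalance that appears is therefore chance, and calling it confounding misnames it. The sound reason to adjust in a randomized trial is that a covariate predicts the outcome, and neither sentence uses that reason. The rule can bring in a covariate that is irrelevant to nocturia and leave out a strong predictor that happens to balance.

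With no criterion and an open set of variables, the primary model is unknown until someone compares the arms at baseline, and the cut-off can be picked at that point. Sex is on the conditional list although it is already a fixed term. The secondary models (Aim 2) and the exploratory models (section {20b}) are to use similar fixed effects, so the rule may spread to them.

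At stake is whether the primary analysis is truly specified in advance. Depending on how the effect is estimated, some precision may be at stake too.

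**Working it through.** **1. The plan's own figure.** Sample size {14} states that "a sample of 192 participants, randomized in equal proportions to the two arms, will provide > 80% power in 2-sided tests" for a difference of 0.7 episodes/night, with under 15% loss. No SD is given, but 0.7 is described as more than half an SD, so SD < 1.4. A simple two-group approximation is power = Φ(δ / (σ√(2/n)) − 1.96).
- 96 per arm, σ = 1.4: 0.7 / (1.4 × √(2/96)) = 3.464, power 0.934.
- 81.6 per arm (15% loss), σ = 1.4: 3.194, power 0.891.
- After 15% loss, power stays above 80% up to σ = 0.7 / (2.8016 × √(2/81.6)) ≈ 1.60.

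The planned mixed-model calculation cannot be reproduced without its variances and correlations, but the claim is consistent with these figures. The covariate rule does not alter the sample size.

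**2. How often the rule fires by chance.** Seven covariates are named; removing sex leaves six. If they are independent and each is flagged with probability p, P(at least one) = 1 − (1 − p)^6.
- p<0.05: 1 − 0.95^6 = 0.265.
- p<0.10: 1 − 0.90^6 = 0.469.
- Standardized difference > 0.2 with 96 per arm: p = 2Φ(−0.2/√(2/96)) = 0.166, giving 0.66.
- Standardized difference > 0.1 with 96 per arm: p = 0.488, giving 0.98.

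The unstated cut-off moves adjustment from occasional to near certain. Correlated covariates would lower these chances, and a longer list (the text allows any baseline covariate) would raise them.

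**3. The planned time-by-group contrast.** Write Y_it = (time and group terms) + βx_i + b_i + e_it, with x_i constant over time. In the change Y_i3 − Y_i1 the term βx_i cancels. With complete data, a main-effect covariate therefore has nothing to act on in this contrast.

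Simulation confirms it. Assumed: 192 participants, three visits, random-intercept model, between-person SD 1.0, residual SD 0.9, six covariates explaining 30% of between-person variance, flag at p<0.10, 1,800 runs (Monte Carlo error of an error rate about 0.005). All runs are under no treatment effect.

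| Covariate form | Predict change? | Dropout | Error rate: if imbalanced / always | Mean SE: if imbalanced / always |
|---|---|---|---|---|
| Main effects | no | 0% | 0.051 / 0.051 | 0.1834 / 0.1834 |
| Main effects | no | 15% | 0.044 / 0.046 | 0.1949 / 0.1946 |
| Main effects | yes | 0% | 0.052 / 0.052 | 0.1907 / 0.1907 |
| Main effects | yes | 15% | 0.047 / 0.048 | 0.2034 / 0.2026 |
| Crossed with time | yes | 0% | 0.039 / 0.052 | 0.1911 / 0.1836 |
| Crossed with time | yes | 15% | 0.052 / 0.057 | 0.2034 / 0.1947 |

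As main effects, the SE changes by well under 1%. With 15% dropout the estimate in a single dataset moved by about 0.03 at most. Crossed with time and predicting change, the SE under the rule is about 4% larger (0.1911/0.1836 = 1.041; 0.2034/0.1947 = 1.045).

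**4. A direct 4-month comparison.** Assumed: 164 analysed, SD 1.4, six independent normal covariates, true difference 0.6 for power, flag at p<0.05, p<0.10, or a standardized difference above 0.1 or 0.2.
- Covariates explain 30% of variance: error rate 0.033–0.041 under the rule against 0.048–0.051 prespecified; mean SE 0.204–0.218 against 0.186; power 0.79–0.85 against about 0.89.
- Covariates explain 10%: error rate 0.042–0.049 against 0.048–0.052; power 0.77–0.80 against 0.80–0.82.

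**5. Where precision is available.** With equal variances and correlation ρ between baseline and 4 months, a change score has variance proportional to 2(1 − ρ), and adjustment for baseline gives 1 − ρ². The SE ratio is √((1 + ρ)/2): 0.922 at ρ = 0.7 and 0.806 at ρ = 0.3. Using baseline nocturia efficiently thus lowers the SE by about 8% to 19%. The range of ρ is an assumption.

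**The case against.** The strongest reply is that the rule is nearly harmless for the analysis as written. Site and sex are unconditional, baseline nocturia is already used as a repeated response, and a time-constant main effect drops out of the time-by-group contrast. That stands. It removes any claim of material power loss for the contrast as defined, unless covariates are crossed with time.

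A reader might infer that a data-driven model inflates false positives. The calculations do not support that: in a direct 4-month comparison the error rate falls below 5%, and with main effects in the planned contrast it is practically unchanged. A reader might also carry over the power gap from the 4-month comparison. That gap belongs to a different estimator and rests on an assumed explained variance that the article does not give.

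It could also be said that an analysis plan may settle the covariates. But this is not a gap left for later. It is a stated rule, given twice, which a plan that fixed the covariates would have to override. And if covariates leave the interaction unchanged, the rule does not deliver the control of confounding that it claims, and adds only discretion.

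**Conclusion.** The rule is badly fixed and should be changed; it is not a must-fix. What holds without further assumptions is that entry depends on observed imbalance, no criterion is stated, the set is open, and prognostic value plays no part. If the six conditional covariates are independent, chance alone triggers the rule in about 26% of trials at p<0.05 and 47% at p<0.10.

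The numerical consequence depends on points that the article leaves open. For the time-by-group contrast with main-effect covariates it is nil with complete data and negligible at 15% dropout. Crossing covariates that predict change with time costs about 4% in SE under the assumptions used; the error rate there is only roughly determined (0.039 with complete data, 0.052 with dropout). A direct 4-month comparison, which the metric in Outcomes {12} could suggest, makes the test conservative and loses precision in proportion to the variance explained.

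The documents do not support reading this as inflation of type I error, as a shortfall in the planned sample size, or as a primary test shown to be invalid.

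**What to change.** - Delete both conditional sentences.
- Fix the model now: site, sex and a short named list of prognostic covariates, or site and sex alone. State how each covariate enters, including any interaction with time.
- Choose only covariates recorded on everyone. Under Recruitment {15}, home sleep apnea testing is limited to people without a prior test who screen as high risk, so sleep apnea status may not be measured alike in all participants.
- Use baseline nocturia efficiently: either constrain the arms to a common baseline mean in the mixed model, or model only post-baseline values with baseline as a covariate. Baseline must not be both a response and a covariate.
- Apply the same covariate set to the secondary and exploratory models.
- Report baseline balance descriptively, and confine imbalance-driven adjustment to a sensitivity analysis.

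The cost is a wording change and a few degrees of freedom. No new data are needed and the sample size stays as it is. Recruitment is expected to run to June 2028, so there is time to do this before the analysis.

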#### Secondary comparative analyses

Aim 2/Hypothesis 2: *Compared to control, participants assigned to integrated nocturia and insomnia behavioral intervention will have greater reduction in self-reported wake after sleep onset and Insomnia Severity Index over the 4-month follow-up period*. Secondary outcomes, patient-reported wake after sleep onset and ISI, will be modeled similarly with a (G)LMM in the original scale or transformed scale as appropriate, where group, time, time*group interaction, and stratified randomization variables (study site and sex) will be included in fixed effects, and random effects will be included for nested clustering by site and participant to account for correlations due to clustering. If the distributions of the secondary outcomes are skewed and no good transformation is found, the outcomes will be categorized into categories based on quantiles or clinically meaningful values and then modeled with GLMMs using cumulative logit or generalized logit link for multinomial data. Similar fixed and random effects will be included in GLMMs. Due to the exploratory feature, no adjustment will be made for the multiple comparisons, but results will be presented as secondary outcome analyses. Secondary analyses similar to those proposed in Aim 1 will be performed on the secondary outcomes of patient-reported wake after sleep onset and ISI.

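### Site, sex and imbalanced baseline covariates are listed without time interactions, so in the linear mixed models they drop almost entirely out of the time×group effect they are meant to adjust

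*Protocol article*

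**What the plan says.** All references are to the Protocol article.

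- **Response.** Under Primary comparative analyses (Aim 1), nocturia is "measured as the average episodes per night at baseline, 1 week after intervention (approximately 2 months), and 4 months". Baseline is therefore one of three repeated responses, not a covariate.
- **Fixed effects.** The model is fitted "with group (the integrated intervention vs. control), time, time*group interaction, and stratified randomization variables (study site and sex) in fixed effects", with "nested two-level random effects to account for correlations due to clustering by study site and participants".
- **Treatment effect.** "The time*group interaction will provide the estimated ITT effect of the integrated intervention on nocturia frequency over time".
- **Imbalanced covariates.** "Imbalanced baseline variables, if any will be included in the LMM". The opening paragraph of the same section says that "they will be included in the (G)LMM fixed effects to control for potential confounding".
- **Reason for adjusting for site and sex.** The same paragraph says that leaving out variables used in the randomization can inflate P values and widen confidence intervals.
- **Other outcomes.** Under Secondary comparative analyses, wake after sleep onset and the ISI use the same structure: "group, time, time*group interaction, and stratified randomization variables (study site and sex) will be included in fixed effects". Methods for additional analyses {20b} applies similar fixed effects to ICIQ-Nqol and PSQI.

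The only interaction named anywhere is time×group.

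**The concern.** The plan gives two reasons for its covariates: precision (site and sex) and control of confounding (imbalanced variables). Both refer to the treatment effect. The effect it names is a difference between arms in change from baseline, and a characteristic fixed at baseline and entered without a time interaction adds the same amount to every visit of a participant. Subtracting baseline from follow-up removes that amount. The terms would then improve the description of level and do essentially nothing for the reported effect.

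Two things are at stake. If site or sex predicts change, stratified randomization reduces the true variance of the estimate but the model's standard error does not show it. If a covariate that predicts change is imbalanced by chance, the resulting shift stays in the estimate while the report says that it was controlled.

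**Working it through.** **Inputs from the protocol.** Three visits and the model terms as listed (Primary comparative analyses); N = 192 allocated 1:1, target difference 0.7 episodes/night, two-sided 5%, power above 80%, loss below 15% (Sample size {14}).

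**The plan's own power figure.** No SD is stated. A two-sample calculation with 96 × 0.85 = 81.6 per arm and a difference of 0.7 gives 89.1% at SD 1.4 and 79.8% at SD 1.6. Since 0.7 is said to exceed half an SD, the implied bound is SD below 1.4, so the claim is plausible but cannot be reproduced exactly. The point here does not depend on it; 80% serves below only as a reference.

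**Step 1: algebra.** With complete data and a time-constant covariate x with coefficient γ, the fitted mean for arm g at visit t is ȳ(g,t) − γ·x̄(g), up to a constant common to all cells. The term γ·x̄(g) does not depend on t. In the difference between arms of [ȳ(g, 4 months) − ȳ(g, baseline)] it cancels, whatever γ is.

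**Step 2: numerical check.** The stated model was fitted by generalized least squares with known covariance to 60 simulated trials per setting (N = 192). Assumptions: true effect −0.70; a covariate shifted 0.4 SD between arms and predicting change; about 15% missing at 4 months where dropout applies. Results for compound symmetry and categorical time:

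| Model | Complete data: mean estimate (SE) | With dropout: mean estimate (SE) |
|---|---|---|
| No covariates | −0.905 (0.1837) | −0.926 (0.1942) |
| Site, sex | −0.905 (0.1837) | −0.927 (0.1943) |
| Site, sex, imbalanced covariate | −0.905 (0.1837) | −0.926 (0.1943) |
| The same, each crossed with time | −0.701 (0.1882) | −0.743 (0.1985) |

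With complete data the first three estimates agreed to about 1e-14. The same held for an unstructured covariance and for linear time. With dropout, the main effects moved a single trial's estimate by at most about 0.04 and the mean by about 0.001. In one further simulated trial fitted by REML with estimated variances, the three models without time interactions all gave −0.9018 (SE 0.1880); crossing with time gave −0.8531 (SE 0.1860).

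**Step 3: cost for site and sex.** Let R² be the share of variance in change that they explain (assumed; the protocol gives none). Stratification makes the true SD of the estimate √(1−R²) times the model's SE. At the 80% reference, effect/SE = 1.960 + 0.8416 = 2.8016. Then:

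- type I error as planned = 2[1 − Φ(1.96/√(1−R²))]
- power as planned = Φ(0.8416/√(1−R²))
- power with covariate×time = Φ(2.8016/√(1−R²) − 1.96)

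| R² | Type I error as planned | Power as planned | Power with covariate×time | Loss (points) |
|---|---|---|---|---|
| 0.02 | 4.8% | 80.2% | 80.8% | 0.5 |
| 0.05 | 4.4% | 80.6% | 82.0% | 1.4 |
| 0.10 | 3.9% | 81.2% | 84.0% | 2.7 |
| 0.15 | 3.4% | 81.9% | 86.0% | 4.0 |

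Losses are taken before rounding. A 5-point loss needs R² of about 0.19.

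**Step 4: an imbalanced covariate.** Assume a binary covariate with 50% prevalence and about 163 participants analysed (192 × 0.85). The SD of the between-arm difference in proportions is √(0.25 × 4/163) = 0.078. A 1.96-SD imbalance is 1.96 × 0.078 = 0.15. With an assumed association with change of 0.5 episodes/night, the shift is 0.15 × 0.5 ≈ 0.08, and 0.08/0.7 ≈ 11% of the target difference. The listed adjustment removes essentially none of it.

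**The case against.** **The form of the covariates is partly inferred.** For imbalanced variables the text says only that they enter the fixed effects, and an unseen SAP could add time interactions. This is true, but the article writes out its model terms, names one interaction and names the contrast. Main effects is the natural reading, and an SAP that copied the text would carry the fault. Outcomes {12} does place the outcome at 4 months, and main effects would act on a plain 4-month group difference, but the Aim 1 paragraph names the interaction as the ITT effect.

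**The harm is small.** This stands. Site and sex are balanced by stratified blocks (Sequence generation {16a}), so the estimate is not shifted and the test errs on the safe side. The change contrast already removes any association that is constant over time. Nothing in the protocol says that a listed covariate predicts change.

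**Stronger readings that the documents do not support.**
- A reader might infer that the primary estimate is biased. Randomization keeps it unbiased on average; what remains is chance imbalance. The −0.905 against −0.70 above shows the mechanism, not the expected size: a 0.4 SD difference at 96 per arm is 0.4/√(2/96) ≈ 2.8 standard errors.
- A reader might compare the adjusted power with a flat 80% and claim losses of 0.8 to 6.0 points. The variance reduction that raises adjusted power also raises power as planned, so the losses are those in the table.
- A reader might extend exact cancellation to every model in the plan. The algebra and the fits cover linear models only, not the cumulative or generalized logit fallbacks for the secondary and exploratory outcomes.

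**Conclusion.** The point holds for the linear mixed models. As listed, site, sex and imbalanced baseline variables leave the time×group estimate and its standard error unchanged with complete data and almost unchanged at the planned dropout, so the two purposes that the plan states are essentially not met for any covariate that predicts change.

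The size is modest: mild conservatism from site and sex, and an uncorrected chance shift from an imbalanced covariate that matters only if that covariate predicts change. These sizes rest on assumed values of R², prevalence and association. The cancellation does not; it rests on reading the listed terms as having no time interaction. It does not invalidate the primary analysis, but the stated rule does not do what the plan says it does, and it should be corrected.

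**What to change.** In Primary comparative analyses, and for the linear models in the secondary and additional analyses, state that site, sex and any other adjustment covariate enter crossed with categorical time (site×time, sex×time, covariate×time), and that the 4-month group contrast from that model is reported.

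An alternative is to model the post-baseline visits with baseline nocturia, site and sex as covariates and report the 4-month group difference. Covariate main effects do act on that contrast. It is not equivalent, because it replaces a difference in change by a baseline-adjusted difference in level, so one of the two should be chosen and named before outcome data are analysed.

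The cost is wording plus a few parameters: two extra per binary covariate with three visits (four for site and sex), and more for multi-category variables such as race/ethnicity or education. Crossing a badly imbalanced covariate with time can also raise the standard error slightly (0.1837 to 0.1882, about 2.4%, in the simulation above). No new data and no change to trial conduct are needed. Recruitment is expected to run to June 2028 and no interim analysis is planned, so there is time.

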### Eligibility criteria {10}

Participant eligibility criteria include the following:

Inclusion criteria: 

Age ≥ 60 yearsAverage of ≥ 2 episodes per night of nocturia on the International Consultation on Incontinence Questionnaire-Overactive Bladder Module (ICIQ-OAB) questionnaireInsomnia Severity Index > 7Able to attend weekly in-person or virtual study visits

Exclusion criteria:

Presence of bipolar disorderSignificant cognitive impairment as measured by a score < 20 on the Mini-Mental State ExaminationSleep disturbance better explained by another sleep disorder such as restless legs syndrome, narcolepsy, insufficient sleep syndrome, or circadian rhythm sleep-wake disordersUntreated sleep-disordered breathing (respiratory event index ≥ 15 plus Epworth Sleepiness Scale > 10, or respiratory event index ≥ 30. Note that participants with treated sleep-disordered breathing are *not* excluded)Current urinary tract infection or hematuria (based on screening urinalysis testing)Unstable doses or recent changes (past month) in medications affecting lower urinary tract symptomsNew or recently discontinued insomnia medication within the past monthPrevious or current intensive behavioral therapy for insomnia or urinary symptomsUnstable health conditions expected to result in death or hospitalization within 3 monthsUnstable medical conditions that could contribute to nocturia or insomnia such as poorly controlled heart failure as evidenced on physical examination, poorly controlled diabetes mellitus with either hemoglobin A1c of ≥ 9.0, or chronic kidney disease (stage 4 or 5) or a potential to initiate dialysis in 3 monthsUnstable psychiatric conditions (e.g., psychosis, active alcohol/substance abuse based on history and medical records)Unstable housing situationEvidence of significant urinary retention (e.g., as measured by a residual bladder volume of ≥ 200 mL by bladder ultrasound or catheterization with 15 min of voiding)Genitourinary cancer undergoing active treatmentPelvic or colon surgery within 6 months of enrollment or onabotulinum toxin therapy for urinary symptoms within 6 months of enrollment

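### The primary mixed model forgoes precision by treating baseline nocturia as a response with a free group difference rather than using it to sharpen the 4-month comparison

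*Protocol article*

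**What the plan says.** In the Protocol article, Primary comparative analyses (Aim 1), the ICIQ-OAB nocturia item is "measured as the average episodes per night at baseline, 1 week after intervention (approximately 2 months), and 4 months". All three occasions feed a linear mixed model "with group (the integrated intervention vs. control), time, time*group interaction, and stratified randomization variables (study site and sex) in fixed effects", plus nested random effects for site and participant. The time-by-group interaction is named as the intention-to-treat effect. Other baseline variables enter only if they turn out imbalanced between arms, and the covariates listed in that section do not include baseline nocturia.

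The Outcomes section fixes the primary outcome at 4 months. Secondary comparative analyses carries the structure to wake after sleep onset and the Insomnia Severity Index, "where group, time, time*group interaction, and stratified randomization variables (study site and sex) will be included in fixed effects", and the section on additional analyses carries it to ICIQ-Nqol and PSQI.

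Under Eligibility criteria, entry requires an average of at least 2 "episodes per night of nocturia on the International Consultation on Incontinence Questionnaire-Overactive Bladder Module", so every participant has a baseline value. Under Sample size, the design "will provide > 80% power in 2-sided tests", and the article attributes that figure to the covariance matrix of the proposed mixed models' regression coefficients.

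**The concern.** Randomization makes the expected baseline means equal in the two arms. A model with baseline as a response and a free group main effect does not use that fact. It estimates a baseline difference known to be zero in expectation and subtracts it from the follow-up difference, which adds the baseline's sampling noise to the treatment estimate. When baseline and follow-up SDs are equal and their correlation is below 0.5, the resulting change-score contrast is less precise than ignoring baseline altogether. Because entry is restricted on the same item, a modest correlation is plausible, though the article gives no value.

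At stake are the width of the confidence interval for the primary effect and the margin by which the trial meets its power target. The plan already adjusts for site and sex on the ground that omitting stratification factors costs precision. The baseline value of the outcome is a natural further candidate.

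**Working it through.** **Inputs.** From Sample size: "we estimate that a sample of 192 participants, randomized in equal proportions to the two arms", so 96 per arm; a two-sided 5% test; a target difference of 0.7 episodes per night; loss below 15%, taken here at 15%, so 96 × 0.85 = 81.6 per arm at 4 months. No SD is stated. The text says only that the effect exceeds half an SD, so SD < 0.7/0.5 = 1.4. No correlation (rho) between baseline and 4 months is stated. Both are therefore varied.

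**The plan's figure.** It cannot be reproduced exactly without the SD and rho, but it is attainable. Power = Φ(0.7 / (S × √(2/81.6)) − 1.96), where S is the SD of the analysed variable. Comparing 4-month values alone at SD 1.4 gives 0.7/0.219 − 1.96 = 1.23, or 89.1%. At SD 1.2 it is 96.1% and at SD 1.0 it is 99.4%. Power is exactly 80% when S = 0.7 / (2.802 × 0.1566) = 1.60.

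**What the model estimates.** With categorical time, a participant random intercept and complete data, the 4-month interaction is the difference between arms in mean change. Site and sex do not vary over time and drop out of the within-person contrast.

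**Variance, equal SDs.** Change score: 2·SD²(1 − rho). Baseline-adjusted: SD²(1 − rho²). The ratio is (1 + rho)/2, so the reduction is (1 − rho)/2: 35%, 30% and 25% at rho 0.3, 0.4 and 0.5.

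**Variance, narrower baseline.** With baseline SD s0 and follow-up SD s1, the change-score variance is s0² + s1² − 2·rho·s0·s1 and the adjusted variance is s1²(1 − rho²). They differ by (s0 − rho·s1)², which is never negative. For assumed values s0 = 0.7 and s1 = 1.1:
- rho 0.3: 1.238 against 1.101, a gain of 11%
- rho 0.4: 1.084 against 1.016, a gain of 6%
- rho 0.5: 0.930 against 0.908, a gain of 2%

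Putting the square roots of these variances in as S gives change-score power of 98.0%, 99.0% and 99.6%, against 98.9%, 99.3% and 99.7% adjusted.

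**Power at the SD ceiling of 1.4, equal SDs.** The three-visit columns use the generalized least squares covariance of the fixed effects, with 7.5% lost before each follow-up visit.

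| rho | Change score | Three-visit model as written | Baseline-adjusted | Three-visit, common baseline mean |
|---|---|---|---|---|
| 0.1 | 66.3% | 69.3% | 89.4% | 89.5% |
| 0.2 | 71.4% | 74.1% | 90.3% | 90.4% |
| 0.3 | 77.0% | 79.3% | 91.7% | 91.9% |
| 0.4 | 83.0% | 84.9% | 93.6% | 93.8% |
| 0.5 | 89.1% | 90.4% | 95.8% | 95.9% |

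**Where power drops below 80%.** The simple change score crosses at rho = 1 − (1.60/SD)²/2: about 0.35 at SD 1.4, 0.25 at SD 1.3 and 0.12 at SD 1.2, and at no rho ≥ 0 when SD is 1.0. The three-visit model as written crosses at about 0.31 at SD 1.4; at SD 1.2 it still has 82.0% at rho 0.1. If the baseline SD is 0.7 times a follow-up SD of 1.4, it has 80.1% at rho 0.1 and 83.9% at rho 0.2. Baseline-adjusted power was never below 89.1% (SD 1.4, rho 0).

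**The case against.** A reader might infer that the trial is underpowered, or that its power calculation belongs to a different model. The article supports neither reading. Falling below 80% needs an SD close to a ceiling that the text itself excludes, loss at its stated upper limit, and a low correlation, all together. The article also says that the power came from the proposed mixed models, for "leading to a between-group difference in improvement in nocturia frequency of 5 or more episodes per week (0.7 episodes/night"). This is the same kind of contrast as the planned interaction, so any efficiency loss should, as described, already be inside the stated figure. That the SD and correlation are not printed is something a journal article may leave to the full protocol.

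A second tempting reading is that restricting entry on the outcome item makes the loss large. The restriction has two effects. It may lower the correlation, but it also shrinks the baseline SD, which reduces the change-score penalty. In the narrowed case worked above, power is about 98% or more with either analysis.

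Finally, a longitudinal mixed model with group, time and their interaction is a standard analysis. It uses all available data, it is unbiased under randomization, and it fits a hypothesis worded as a greater reduction. All of these objections stand. They limit the size and seriousness of the point but do not remove it: the baseline value is available for everyone, and in these calculations using it never loses precision.

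**Conclusion.** The point holds as a recommended precision improvement. It does not correct bias, type I error or a demonstrated power shortfall. As written, the 4-month effect is in essence a comparison of changes from baseline, and baseline nocturia has no planned role as a covariate. Its variance could be lowered by 25% to 35% for rho between 0.5 and 0.3 if the SDs are equal, and by 2% to 11% over the same range if the baseline SD is 0.7 against 1.1. At SD 1.4, power rises by about 13 points at rho 0.3 and 5 to 6 points at rho 0.5 (three-visit model). At smaller SDs the gain in power is smaller.

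These sizes rest on assumed SDs and correlations, 15% loss, and a reading of the nested random effects as random intercepts. The same model structure applies to the secondary and exploratory outcomes. The size of the gain there was not calculated, because the article gives no SDs or correlations for them.

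**What to change.** Prespecify a model whose responses are the post-treatment and 4-month values, with baseline ICIQ-OAB nocturia and its interaction with visit as covariates, alongside group, visit, group-by-visit, site and sex. Alternatively, keep baseline as a response but drop the group difference at baseline, so that both arms share one baseline mean. The two options perform almost identically here (91.7% and 91.9% at SD 1.4, rho 0.3), so the choice is a matter of convenience. In either case, name the 4-month group contrast as the primary effect, and use the same form for wake after sleep onset, Insomnia Severity Index, ICIQ-Nqol and PSQI. Stating the SD and correlation behind the power figure would let a reader check it.

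The cost is one model statement per outcome. Baseline is already collected, no sample size change is needed, and recruitment is expected to run to June 2028, so the change can be fixed before the analysis.
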